## **Data**

Specially designated case record forms (CRFs) will be used for continuous registration.

Data from the case record forms will be entered into the database and then be coded (pseudonymized).

One person at each hospital is responsible for the recording of information into the database, and only this person is familiar with the code key. Approval from The Data Inspectorate for the registration of information for all patients operated for obesity at OUH is granted.

### **Statistical methods**

For between-group comparisons, Mann-Whitney U test and Wilcoxon's test will be used for non-parametric data, and Student's *t* test and paired *t* test for parametric analysis. Dichotomous outcome variables will be analyzed with chi-square test or Fisher's exact test as appropriate.

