### **3. Material**

#### **Inclusion criteria:**

Patients scheduled for surgery for morbid obesity with a BMI of 50 – 60 at referral (48 – 62 at inclusion).

Age 20 to 50 years.

Signed informed consent.

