### **4. Methods**

#### **Study design:**

Two-center, prospective, randomized trial.

Relevant parameters are registered prospectively in designated form (Case Record Form).

Each patient is his own control regarding the above-mentioned end points.

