#### **Analytical methods:**

*Weight loss evaluated before and 1½, 6, 12, 24 and 60 months after surgery:*

Weight, BMI, and percentage weight lost.

*Body composition evaluated before and 12 and 24 months after surgery:*

Waist and hip circumferences and sagittal abdominal diameter.

Segmental bioelectrical impedance analysis in Norwegian participants. 40K spectroscopy in Swedish participants.

*Quality of life evaluated by the following questionnaires before and 12, 24 and 60 months after surgery:*

Short Form 36 health survey (SF-36).

The Obesity-related problems scale (OP-scale).

Gastrointestinal quality of life (GSRS).

Questionnaire on bowel function ("Frågeformulär tarmfunktion").

*Eating pattern (measured at similar time points):*

Three factor eating questionnaire (TFEQ).

Four-day dietary record.

Additional questions about diet and supplements.

*Health economics:*

The use of disposable surgical equipment.

Lengths of surgery and anesthesia.

Lengths of stay in post-operative department and in intensive care unit.

Length of hospital stay (expenses are converted into costs in NOK or Euros by current method applied at Sahlgrenska).

Number of visits in primary care and outpatient clinics because of obesity - before and after surgery.

*Associated diseases evaluated before and 12, 24 and 60 months after surgery:*

Diabetes: Measurement of fasting plasma glucose and insulin and record of any use of antidiabetic drugs.

Hypertension: Measurement of blood pressure and the need for medication.

Dyslipidemia: Measurement of lipids and the need for medication.

*Complications:*

Recording of early complications (within 30 days after surgery) such as anastomotic leak, hemorrhage demanding surgical intervention, pulmonary embolism, abscess, reoperations, and death etc. Further registration of late (>30-day) complications at outpatient visits.

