### **Sample size**

Sample size calculation is based on change in weight. In a retrospective study from Sahlgrenska, mean (SD) reductions in BMI for super-obese patients 3 years after surgery were 24.9 (5.0) after duodenal switch (*n*=13) and 18.0 (6.7) after gastric bypass (*n*=19). Thus, 60 study participants would give >90% power to detect a difference in the change in BMI between groups (2-sided *t* test, *P*=.05).

Regarding quality of life, we expect that a 15% difference in score between the groups is clinically significant.

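### The protocol fixes unadjusted two-sample tests for a weight end point measured at baseline and five later visits in two centres; they are valid but less precise than a baseline-adjusted repeated-measures model

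*Protocol*

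**What the plan says.** The Statistical methods paragraph (Protocol, section 4) is the protocol's whole analysis text. For continuous outcomes it states "For between-group comparisons, Mann-Whitney U test and Wilcoxon's test will be used for non-parametric data", with Student's t and paired t tests for parametric analysis. For binary outcomes, "Dichotomous outcome variables will be analyzed with chi-square test or Fisher's exact test as appropriate". The paragraph mentions no covariate, centre term or model across visits.

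Other sections describe the data that will be available:

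- Design: "Two-center, prospective, randomized trial".
- Visits: "Weight loss evaluated before and 1½, 6, 12, 24 and 60 months after surgery".
- Eligibility: patients scheduled for surgery "with a BMI of 50 – 60 at referral (48 – 62 at inclusion").
- Sample size: "60 study participants would give >90% power to detect a difference in the change in BMI between groups" ("2-sided *t* test, *P*=.05"). The powered outcome is therefore a change score.
- Section 2: the primary end point is long-term weight reduction and weight stability. The alternative hypotheses include a 10–20% greater loss at two years after duodenal switch, and a difference in regain after that.

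**The concern.** The end point concerns the course of weight over years, but the named tests compare one value per patient and set aside information the trial already collects.

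- **Baseline BMI.** It spans 14 units at inclusion (48 to 62), and the absolute fall in BMI plausibly depends on where a patient starts. Subtracting baseline does not in general remove that dependence; a covariate does.
- **Centre.** Two hospitals in two countries operate, and any difference between them in average weight loss stays in the error term.
- **Earlier visits.** A patient who is not weighed at 60 months may have four earlier postoperative weights. Without imputation, a t or rank test at 60 months cannot use them.

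At stake are the width of the confidence interval and the power for differences smaller than the design effect. The third item also affects how well the 5-year comparison stands up if follow-up is incomplete.

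**Working it through.** **Inputs from the protocol.** Sample size section: mean (SD) BMI reductions of "24.9 (5.0) after duodenal switch (*n*=13) and 18.0 (6.7) after gastric bypass (*n*=19"), total 60, two-sided 5% level. Alternative hypotheses: 10–20% greater loss.

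**Assumptions.** Allocation is 1:1, so 30 per arm (the ratio is not stated). The correlation r between baseline BMI and BMI change is not in the documents; 0 to 0.5 is shown. The 10–20% is applied to the gastric bypass mean of 18.0, although the hypothesis refers to two years and that mean to three.

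**Step 1: the protocol's own figure.**
- Difference = 24.9 − 18.0 = 6.9 units.
- SD weighted by group size = √[(12 × 5.0² + 18 × 6.7²)/30] = 6.08.
- SD with equal weights = √[(5.0² + 6.7²)/2] = 5.91.
- Power of the two-sample t test (noncentral t) = 99.1% with SD 6.08 and 99.4% with SD 5.91. With 6.7 in both arms it is 97.5%.

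The stated figure of over 90% is reproduced.

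**Step 2: baseline BMI as a covariate.** The residual SD is SD × √(1 − r²), so the standard error is SD × √(1 − r²) × √(2/30). With SD 5.91:

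| r | 1 − r² | Standard error | Power, 6.9 units | Power, 3.6 units | Power, 1.8 units |
|---|---|---|---|---|---|
| 0 (unadjusted) | 1.00 | 1.53 | 99.4% | 64% | 21% |
| 0.3 | 0.91 | 1.46 | 99.7% | 68% | 23% |
| 0.5 | 0.75 | 1.32 | 99.9% | 76% | 27% |

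Here 3.6 = 0.20 × 18.0 and 1.8 = 0.10 × 18.0. With SD 6.08, power at 3.6 units is 62% unadjusted, 66% at r = 0.3 and 74% at r = 0.5. Across both SDs, power goes from 62–64% to 66–76%.

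At r = 0.3, 60 × 0.91 ≈ 55 patients analysed with adjustment give the precision of 60 without it. At r = 0.5 the number is 60 × 0.75 = 45.

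**Step 3: centre.** With equal numbers per centre, a difference of c units in mean BMI change between centres accounts for (c²/4)/5.91² of the variance: 0.7%, 2.9% and 6.4% for c = 1, 2 and 3. Unless the centres differ a good deal, most of the gain comes from baseline BMI.

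**Step 4: missing 60-month weights.** The protocol gives no dropout rate. If 10%, 20%, 30% or 40% are missing (27, 24, 21 or 18 left per arm, SD 5.91), the unadjusted t test on those measured has:
- for 6.9 units: 98.8%, 97.7%, 95.8% and 92.5% power;
- for 3.6 units: 59%, 54%, 49% and 43% power.

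For the design effect, then, missing data threaten power little. The larger question is whether patients who stay away differ in weight course. A mixed model uses their earlier weights and is valid if data are missing at random. A test on those measured at 60 months takes no account of those weights.

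**The case against.** The case for leaving the tests as they are is substantial. In a randomised trial the unadjusted t and rank tests are valid, and at the protocol's own effect size adjustment changes nothing that matters: power is about 99% either way. The gain at 3.6 units depends on a correlation the documents do not give. Adjustment also leaves power at 66–76% there and at 23–27% for 1.8 units, so it does not make the trial large enough for the smaller effects. All of this stands and limits the point to precision.

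A reader might infer four stronger things, and the protocol supports none of them.

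- **That baseline BMI is ignored.** It is not. The powered outcome is change in BMI, and percentage weight lost is also recorded, so baseline enters by subtraction or ratio. Only its use as a covariate is absent.
- **That the 5-year result is restricted to completers.** No section says so. The protocol has no missing-data rule, and a statistical analysis plan that is not shown may set one. What can be said is conditional: without imputation, a single-visit test uses only those measured at that visit.
- **That chance imbalance in baseline BMI or centre biases the comparison.** It does not. Over repeated randomisations the estimate is unbiased, and the standard error already allows for such imbalance. Adjustment removes part of that variability.
- **That the choice between t and Mann-Whitney is made after seeing the data.** The protocol gives no rule for the choice, but the sample size section names the t test for BMI change, and an analysis plan may hold the rule.

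The objection does not remove the core. This is a stated choice of tests and not a detail left open, and a better choice is available from data already collected.

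**Conclusion.** The point holds as a matter of efficiency. The protocol fixes tests that are valid but use less of the collected data than they could. For r between 0.3 and 0.5 the standard error falls by about 5–13% (1.53 to 1.46–1.32 units), and power at 3.6 units rises by roughly 4 to 12 percentage points. If r is 0, adjusting for baseline gains nothing. The conclusion about the 6.9-unit design effect is unaffected.

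These figures assume 1:1 allocation, the retrospective SDs and the reading of 20% against 18.0. If the SD were 6.7 in both arms, unadjusted power at 3.6 units would be 53%. The benefit of using earlier visits arises where later weights are missing, and cannot be sized without a dropout rate.

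**What to change.** In Statistical methods, make the primary weight analysis a linear mixed model of BMI change at all scheduled postoperative visits. Include treatment, visit, treatment-by-visit, baseline BMI, baseline-by-visit and centre. Report the between-group difference with a 95% confidence interval at 24 and 60 months. Use baseline- and centre-adjusted models for the continuous questionnaire scores, and keep the t or Mann-Whitney test as a sensitivity analysis.

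Body composition needs separate thought. It is measured by impedance in Norway and by 40K spectroscopy in Sweden, and a centre term would absorb only a constant shift between the two methods.

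The cost is a little more analysis work and no new data. The mixed model relies on missing-at-random, which should be stated alongside it.

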## **2. Aims of the study**

To compare treatment outcome in super-obese (BMI 50-60), aged 20-50 years at inclusion, after:

- Laparoscopic gastric bypass with a long (150 cm) alimentary limb (long limb laparoscopic gastric bypass).
- Laparoscopic biliopancreatic diversion with duodenal switch (alimentary limb 200 cm and common channel 100 cm).

Primary end point: Long-term results regarding weight reduction and weight stability

Secondary end points: Long-term results regarding quality of eating and quality of life  
Per- and postoperative complications  
Postoperative mobilization and length of hospital stay  
Long-term complications (including surgical revisions)  
Changes in body composition  
Nutritional deficiencies after surgery  
Demand for hospital services (i.e. operating costs, outpatient visits)  
Long-term results regarding eating disorders  
Changes in comorbidities

Based on the same data set, more detailed studies regarding the nutritional consequences of surgery for obesity will be carried out. This is defined in more detail in a separate research protocol with the principal research fellow [name] and professor [name], Department of Medicine, Oslo University Hospital Aker.

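### The only test rule for continuous outcomes would send skewed monetary costs to a rank test, which does not compare mean cost per patient

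*Protocol*

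**What the plan says.** Section 2 (Aims of the study) lists among the secondary end points "Demand for hospital services (i.e. operating costs, outpatient visits". Section 4, Analytical methods, Health economics, names the components: disposable equipment, surgery and anesthesia times, "Lengths of stay in post-operative department and in intensive care unit", hospital stay, and visits because of obesity. With the item on hospital stay it adds that "expenses are converted into costs in NOK or Euros by current method applied at Sahlgrenska".

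Section 4, Statistical methods, is the only analysis rule in the protocol. For outcomes that are not dichotomous it has two branches: "Mann-Whitney U test and Wilcoxon's test will be used for non-parametric data", and "Student's *t* test and paired *t* test for parametric analysis". It does not mention cost, does not define when data count as non-parametric, and does not ask for an estimate with an interval.

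**The concern.** Total spend on a procedure is the number of patients treated times the mean cost per patient, so the mean is the natural quantity for a monetary comparison. Costs built from theatre time, intensive care and hospital stay are typically right-skewed, because a few complicated courses are very expensive. The usual reading of the two-branch rule puts such data in the rank branch.

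The Mann-Whitney test asks whether a random patient in one arm tends to cost more than a random patient in the other. A stay that costs five times the usual amount and one that costs fifty times as much receive nearly the same top rank. The test therefore answers a different question from the one that a monetary comparison raises, and its p value comes with no mean cost difference or interval. An SAP that simply followed the protocol's rule would inherit this.

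**Working it through.** **1. The plan's own figure.** The only power statement is that "60 study participants would give >90% power to detect a difference in the change in BMI between groups". Inputs are the BMI reductions under Sample size, "24.9 (5.0) after duodenal switch" and "18.0 (6.7) after gastric bypass", with a two-sided 5% level. I assume 1:1 allocation, 30 per arm.

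- Difference: 24.9 − 18.0 = 6.9.
- Root-mean-square SD: √((5.0² + 6.7²)/2) = √34.945 = 5.91.
- Noncentrality: 6.9 / (5.91 × √(2/30)) = 4.52, which gives power of about 99% on 58 degrees of freedom.
- With the pooled SD of 6.08, power is about 99%. With the larger SD of 6.7 it is about 98%.

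The stated figure reproduces. It concerns BMI and says nothing about cost.

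**2. Illustration for cost, first model.** The protocol gives no cost distribution, so every input here except the arm size is an assumption. Base cost is log-normal with a coefficient of variation of 20%. A complicated case costs 5 times as much. Complication rates are 15% in arm A and 3% in arm B. There are 30 patients per arm.

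With relative base cost m and complication rate p, mean cost = m × (1 + (5 − 1)p) = m × (1 + 4p). Arm B: 1 + 4 × 0.03 = 1.12. Arm A: m × (1 + 4 × 0.15) = 1.60m. Rejection rates are simulated; with 4,000 trials the Monte Carlo standard error is at most √(0.25/4000) = 0.8 percentage points.

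| Base cost in A relative to B | Mean ratio A/B | Mann-Whitney rejects | Welch t test on means rejects |
|---|---|---|---|
| 15% lower | 1.36/1.12 = 1.21 | 36%, virtually all calling A cheaper | calls A cheaper in 0.6% |
| 5% lower | 1.52/1.12 = 1.36 | 5% | 24% |
| equal | 1.60/1.12 = 1.43 | 12% | 32% |
| 10% higher | 1.76/1.12 = 1.57 | 64% | 50% |
| 15% higher | 1.84/1.12 = 1.64 | 86% | 60% |
| 20% higher | 1.92/1.12 = 1.71 | 96% | 66% |

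In the second row the chance that a random A patient costs more than a random B patient is 0.50. The rank test therefore sees no difference at all, although mean cost is 36% higher in A. With milder rates of 10% versus 5% and equal base cost, the mean ratio is 1.40/1.20 = 1.17, and the two tests reject in about 5% and 8% of trials.

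**3. Second model, to test sensitivity.** Base cost has a coefficient of variation of 25%. A complication adds a log-normal cost that averages 8 times the base cost. Rates are 15% versus 5%, with 30 per arm and 10,000 trials. Mean cost = m + 8p.

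- Equal base cost: 2.20 versus 1.40, ratio 1.57. Rejection in the right direction: Mann-Whitney 10%, Welch 12%.
- Base cost in A 15% lower: 2.05 versus 1.40. Mann-Whitney significantly calls A cheaper in 24%, Welch in under 1%.
- Base cost in A 20% lower: 2.00 versus 1.40. Mann-Whitney calls A cheaper in 48%, Welch in under 1%.
- Base cost in A 30% higher: 2.50 versus 1.40. Mann-Whitney rejects in 97%, Welch in 35%.

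**4. Reading.** Across both models the rank test follows the typical patient and is nearly blind to how expensive the tail is. Whether it rejects more or less often than a comparison of means depends on the base cost, which the protocol does not give.

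**The case against.** **The rule does not name cost.** It is a generic list of tests, and how a secondary cost outcome is analysed is commonly settled in an SAP that is not shown. That stands in part. Assigning cost to the rank branch is an inference, and an analyst could class cost under the t test. But the point is not that detail is missing. The protocol states a rule with only two branches, and on its ordinary reading that rule suits one of the plan's own end points badly.

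**A reader might infer that the trial is likely to miss a cost difference or report it backwards.** The documents do not support that:

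- Reversal needs the arm with more complications to be cheaper in routine cases. The Background calls duodenal switch technically more challenging and possibly higher in morbidity, so both cost drivers probably point the same way. In that direction the rank test rejects more often than the comparison of means (64% versus 50% at a 10% higher base cost), with no rejections in the wrong direction.
- The low power is not the rank test's fault alone. With about 30 per arm a test on means is also weak: 12% against 10% in the second model with equal base cost.

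**A reader might also infer that the protocol expects leaks, reoperations or intensive care to differ between arms.** It does not. The Hypotheses in section 2 state similar perioperative and late complications. The Alternative hypotheses name weight, gastrointestinal side effects and nutritional disorders. The Background's remarks on morbidity are hedged and stress long-term malabsorption. The rates and cost multipliers used above are illustrations only.

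**Resource items are not money.** For lengths of stay, operating times and visit counts a rank test is a defensible choice, and the protocol states no budget or cost-effectiveness aim. That stands, and it limits the point to monetary costs.

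**Conclusion.** The point holds in a limited form: for monetary costs, the rule as written targets the wrong quantity. It would test rank ordering and would leave the report without a mean cost difference and its uncertainty. This rests on two assumptions: that costs are right-skewed, as is typical, and that skewed data are what the protocol means by non-parametric data.

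The practical size cannot be read from the protocol. Under the assumed inputs, rejection by the rank test ranged from 5% to 97% while the arm with more complications always had the higher mean cost. It was sometimes well below and sometimes well above the rate for a comparison of means. A likely miss or a likely reversal is not established. The matter is minor: cost is one of several secondary end points, and neither the weight analysis nor the sample size is touched.

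**What to change.** Add one sentence to Statistical methods: monetary costs are compared as arithmetic means whatever their distribution, with the mean difference and a bootstrap 95% confidence interval resampled within arm; medians and any Mann-Whitney result for cost are descriptive or supportive only. Length of stay, operating time and visit counts may stay under the existing rule.

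The cost is one sentence and a few lines of code. The downside is a wide interval with about 30 patients per arm, which states correctly how little a trial of this size can say about mean cost. The gain is in the quantity reported, not in power.

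### For yes/no comorbidity change the protocol names only unpaired, unadjusted tests, although each patient's baseline status is recorded: a modest loss of power on one secondary end point

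*Protocol*

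**What the plan says.** The Statistical methods section of the Protocol has two sentences. The first covers continuous data. It opens with "For between-group comparisons, Mann-Whitney U test and Wilcoxon's test will be used for non-parametric data" and continues with "Student's *t* test and paired *t* test for parametric analysis", so it names paired as well as unpaired tests. The second covers every yes/no outcome with one rule: "Dichotomous outcome variables will be analyzed with chi-square test or Fisher's exact test as appropriate". It names no paired test and no baseline-stratified or adjusted method.

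Three other places bear on this:

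- Section 2 (Aims of the study) lists "Changes in comorbidities" among the secondary end points.
- Section 4, Study design, says: "Each patient is his own control regarding the above-mentioned end points".
- Section 4, Analytical methods, has "Associated diseases evaluated before and 12, 24 and 60 months after surgery". For diabetes this includes a "record of any use of antidiabetic drugs"; for hypertension and dyslipidemia it includes the need for medication.

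The Protocol does not say how comorbidity change is coded: status at follow-up, remission among those affected, or a shift from baseline.

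**The concern.** The end point is a change and the data are repeated readings on the same patients, but the only tests named for yes/no data take no account of a patient's earlier reading unless the analysis set or the outcome is defined to do so. There are two possible consequences.

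- **Within an arm, before versus after.** A chi-square or Fisher table treats the two readings of one patient as two patients. The correlation between them is lost, the error term is too large, and a real change can be missed.
- **Between arms at follow-up, all patients counted.** Patients free of the disease at baseline cannot remit and dilute the contrast, and chance differences in baseline prevalence add noise.

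Both cost power on an end point for which 60 patients already give little.

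**Working it through.** **1. The plan's own figure.** The Sample size section says "60 study participants would give >90% power to detect a difference in the change in BMI between groups". Inputs from that section: BMI reductions of 24.9 (SD 5.0, n=13) and 18.0 (SD 6.7, n=19), two-sided 0.05. Allocation is not stated, so 30 per arm is assumed.

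- Difference = 24.9 − 18.0 = 6.9.
- Pooled SD = √[(12×5.0² + 18×6.7²)/30] = 6.08.
- SE = 6.08 × √(2/30) = 1.57; 6.9/1.57 = 4.40.
- Power = Φ(4.40 − 1.96), about 99% (99.1% with the noncentral t; 97.5% if the SD is 6.7).

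The stated power is right, and it does not concern the yes/no comorbidity analysis.

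**2. Before versus after within one arm.** The Protocol gives no comorbidity rates, so this is an illustration: 30 patients, 12 affected before and 6 after, with 6 remissions and no new cases.

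- Chi-square, readings treated as independent: pooled proportion 18/60 = 0.30; SE = √(0.30×0.70×2/30) = 0.118; z = 0.20/0.118 = 1.69; P = 0.091.
- Fisher's exact: P = 0.158.
- Exact McNemar on the 6 patients who changed, all in one direction: P = 2×(1/2)⁶ = 0.031.

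The source of the gap is the variance of the difference. Unpaired it is (0.4×0.6 + 0.2×0.8)/30 = 0.0133, SE 0.115. Paired it is (6 − 6²/30)/30² = 0.0053, SE 0.073.

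The conclusion at 5% does not always flip. For 10/30 falling to 3/30 with 7 remissions and no new cases, chi-square gives 0.028, Fisher 0.057 and exact McNemar 2×(1/2)⁷ = 0.016.

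Simulated power within one arm (n=30, 2% new cases, 20,000 runs; all rates assumed):

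| Baseline prevalence | Remission | Unpaired Fisher | Exact McNemar |
|---|---|---|---|
| 30% | 50% | 6% | 22% |
| 30% | 80% | 49% | 63% |
| 50% | 50% | 32% | 70% |
| 50% | 80% | 93% | 97% |

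**3. Between arms at follow-up.** Assumed: 30 per arm, 40% affected at baseline, 20% versus 60% of those still affected, 2% new cases. Expected follow-up prevalence is 0.4×0.2 + 0.6×0.02 = 9.2% in one arm and 0.4×0.6 + 0.6×0.02 = 25.2% in the other. Simulated power:

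| Analysis | Power |
|---|---|
| Chi-square, follow-up status, all patients | 38% |
| Cochran-Mantel-Haenszel, stratified by baseline status | 47% |
| Chi-square, remission among those affected at baseline | 54% |
| Fisher, remission among those affected at baseline | about 42% |

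Over baseline prevalence of 30-60% and persistence of 20% vs 50%, 20% vs 60% and 10% vs 50%, stratifying gains about 2 to 10 points over chi-square in all patients. With no arm effect, chi-square in all patients and the stratified test both reject in about 5% of trials. Chi-square restricted to those affected rejects in about 5-6%, so part of its advantage may be a slightly raised size.

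**The case against.** A reader might infer that chi-square and Fisher cannot use baseline status at all. The text does not support that. It fixes the test, not the outcome variable or the denominator. Remission among patients affected at baseline can be tested by either, uses baseline status, and with chi-square did at least about as well as the stratified test in the simulation. What remains is that the Protocol does not say this is the analysis intended, and the candidate analyses differ appreciably in power (38% to 54% in the case above).

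A reader might also infer that chance baseline imbalance biases the comparison of arms. It does not. Randomization keeps the unadjusted test valid, at a size of about 5%. Imbalance is ordinary sampling error already allowed for in the P value, and the cost is precision.

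Nor does the Protocol expressly say that before-after yes/no data will go into a chi-square table. The paragraph opens with between-group comparisons, and the hypotheses in section 2 are contrasts between the two operations. Against this, the first sentence goes on to list paired tests, and Study design calls patients their own controls, so within-patient comparison is evidently contemplated. The point about pairing is therefore conditional on such a comparison being made.

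The scope is narrow. Glucose, insulin, blood pressure and lipids are continuous and have paired tests. Complications and revisions have no baseline value, and chi-square or Fisher suits them. A statistical analysis plan, not available here, may settle the rest. It would still have to depart from or add to a method that the Protocol has already named.

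**Conclusion.** The point holds as a minor one. The tests named for yes/no outcomes fit poorly with an end point defined as change in patients whose baseline status is known. Used before versus after within an arm, they can lose substantial power (32% against 70% at 50% prevalence and 50% remission). Used between arms on follow-up status in everyone, they are valid and lose about 2 to 10 power points against a baseline-stratified test. These sizes rest on assumed prevalence, remission and new-case rates and on 30 patients per arm, none of which the Protocol states. One secondary end point is affected, and only its yes/no components: medication use or need, and any disease-status classification. The primary weight analysis and the sample size stand.

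**What to change.** Add to the Statistical methods section:

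- For any within-arm before-after comparison of a yes/no outcome, use the exact McNemar test.
- For between-arm comorbidity change at each follow-up visit, use a comparison stratified by or adjusted for the patient's baseline status (Mantel-Haenszel, or exact or penalised logistic regression if cells are sparse), with a risk difference and 95% confidence interval.
- Alongside it, report remission among patients affected at baseline, with that denominator stated. Chi-square or Fisher's exact test is suitable here.

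The cost is a few lines of wording and no new data. The one drawback is that with about 30 patients per arm some strata will be sparse, which is why an exact or penalised method should be named in advance.
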